
### Treatments

2.3

Cobimetinib (provided by Hoffmann-La Roche) is an oral selective inhibitor of the MEK pathway. Vemurafenib (provided by Hoffmann-La Roche) is a low-molecular-weight inhibitor of BRAF serine–threonine kinase. Atezolizumab (provided by Hoffmann-La Roche) is an anti-PD-L1 antibody.

The study will include three possible treatments: (1) vemurafenib 960 mg twice daily per os from day 1 to 42; (2) vemurafenib 720 mg twice daily per os from day 1 to 42; (3) cobimetinib 60 mg once daily per os from day 1 to 21 and from day 29 to 42; cobimetinib should not be taken on days 22–28; and (4) atezolizumab 840 mg intravenous for two cycles (days 22 and 43).

Patients will be randomized to three different arms: A) *BRAF*-mutated patients will receive (1) + (3) for 6 weeks; B) *BRAF*-mutated patients will receive (2) + (3) + (4) for 6 weeks; C) *BRAF* WT patients will receive (3) + (4) for 6 weeks.

All patients will also receive atezolizumab 1200 mg intravenous every 3 weeks for 17 cycles after surgery and after a second screening period (up to 6 weeks).

### Endpoints and assessments

2.4

Endpoints are reported in **Table 2**. The primary endpoint will be the pCR, defined as residual cancer burden = 0.

**Table 2 T2:** Study endpoints.

Primary endpoint	
•To determine the pCR rate
Secondary endpoints
•Recurrence-free survival at 2 years, 3 years, and at the end of the study. Recurrence-free survival is defined as the time from randomization to recurrence event (local or distant disease development or death). •Overall survival is defined as the time from randomization to death. •Pathological overall response rate is defined as the sum of pCR, near pCRs and pathologic partial responses. •Safety: frequency of the following treatment-emergent AEs while on treatment or within 30 days after the last study treatment: All AEs, grade 3–5 AEs, serious AEs, AEs of special interest, and AEs leading to treatment discontinuation or withdrawal from the study. •To determine molecular and immunophenotypic changes in tumor and peripheral blood by evaluating several biomarkers. Since identifying new markers for immunotherapy is rapidly evolving, the definitive list of analyses remains to be determined. The following tests are suggested (differences: baseline, during the adjuvant treatment at week 6, surgical time points, and at recurrence will be compared): •Immunoscore (densities of tumor-infiltrating CD3 and CD8 cells), as well as PD-L1 expression on tumor and immune cells, evaluated by immunohistochemical analysis with an automated quantification system and a standardized assay on tumor tissue •Circulating cytokines and chemokines profiling, evaluated by Luminex technology in patient peripheral blood samples •Myeloid-derived suppressors cells and immune cell subtypes expression and lymphocyte activation, evaluated by multicolor cytofluorimetric approach in patient peripheral blood samples •Metabolomic profiling in patient peripheral blood samples, evaluated by nuclear magnetic resonance Spectrometer (600 MHz) •Tumor mutational burden by whole-exome sequencing on tumor and matched normal tissue at baseline. •Additional analysis of protein levels (i.e., CCR5), DNA mutations, and/or mRNA analysis to enable molecular classification (e.g., CMS), as well as other exploratory markers related to immunotherapy in tumor tissues

AE: Adverse event; pCR: Pathologic complete response.

Secondary endpoints will include recurrence-free survival at 2 years, 3 years and at the end of the study, defined as the time from randomization to recurrence event (local or distant disease development or death); patients without events at the end of the study period, who will be censored at the date of the last follow-up. OS is defined as the time from randomization to death; for patients alive at the end of the study, time will be censored at the date of the last follow-up. Pathological overall response rate is defined as the sum of pCRs, near pCRs and pathologic partial responses. Frequency of treatment-emergent adverse events (AEs) will be assessed during treatment or within 30 days after the last study treatment (all AEs, grade 3–5 AEs, serious AEs, AEs of special interest, and AEs leading to treatment discontinuation or withdrawal from the study). Molecular and immunophenotypic changes in the tumor and the peripheral blood will be evaluated by assessing biomarkers at baseline, during the adjuvant treatment at week 12 surgical time points, and recurrence. The list of markers will be completed based on updated evidence. At the time this protocol is prepared, the following biomarkers are envisaged: Immunoscore (densities of tumor-infiltrating CD3 and CD8 cells) and PD-L1 expression on tumor and immune cells, evaluated by immunohistochemical analysis with an automated quantification system and a standardized assay on tumor tissue; circulating cytokines and chemokines profiling, evaluated by the Multiplex Luminex technology (Luminex, Austin, TX, USA) in peripheral blood samples; myeloid-derived suppressor cells and immune cell subtypes expression and lymphocyte activation, evaluated by a multicolor cytofluorimetric approach in patient peripheral blood samples; metabolomic profiling in patient peripheral blood samples, evaluated by 1H-NMR (proton nuclear magnetic resonance) using a Bruker Avance 600 NMR spectrometer operated at a 599.97 MH; tumor mutational burden by whole-exome sequencing on tumor and matched normal tissue at baseline. Additional analysis of protein levels (i.e., CCR5), DNA mutations, and/or mRNA analysis is planned to enable molecular classification (e.g., CMS) and other exploratory markers related to immunotherapy in tumor tissues.

Some biomarkers and parameters proposed as potential predictive biomarkers for immunotherapy (i.e., C-reactive protein; LDH; absolute neutrophil, monocyte, eosinophil, and lymphocyte counts) will be correlated with pathological response and patient outcome.

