### Data analysis

2.6

All enrolled patients receiving at least one dose of the study medication will be considered the intention-to-treat population (ITT). The patient subgroup of the ITT population receiving at least one dose of the study drug will define the safety population. The analysis of efficacy endpoints will be performed in the ITT population, whereas the safety analysis will be performed in the safety population. A primary data analysis assessing the primary endpoint will be available after the neoadjuvant phase. A final data analysis will be available at study closure. The safety analysis will be completed within 12 months from the last visit of the last patient.

Primary endpoint results will be reported as counts and rates with confidence intervals. No comparisons among arms are planned. Demographical and clinical characteristics will be presented as descriptive statistics and summarized according to the treatment arm. Categorical variables will be given as counts and percentages, quantitative ones as mean and standard deviation, or median and interquartile range, as appropriate. No adjustment for multiple testing will be made.

Safety and tolerability will be assessed regarding AEs, laboratory data, ECG data, vital signs, and weight, which will be collected for all patients. AEs [both in terms of MedDRA preferred terms (26) and CTCAE 5.0 grade (27)], laboratory data, ECG data, vital signs data, and weight will be listed individually by the patient and summarized. Prevalence of related AEs, by grade, will be presented with a 95% CI. Survival will be represented with Kaplan-Meier curves, from which the median with 95% CIs will be derived.

Due to the small sample size, statistical analysis of biomarkers data will be conducted with the aim of hypothesis generation. A complete description of the data will be done. For biomarkers that might change over time due to treatment, levels before and after treatment will be compared with appropriate statistical tests based on the data type. Correlation with outcomes will be evaluated with univariate regression models. p ≤ 0.05 will be considered significant, and no adjustment is planned for multiple comparisons due to the exploratory nature of the analysis.

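### Markers put forward as predictive for immunotherapy are related to pathological response without setting arm A apart, although arm A's response is reached before any atezolizumab

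*Protocol article*

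**What the plan says.** Protocol article, section 2.4 (Endpoints and assessments), names C-reactive protein, LDH and several blood counts as examples of "Some biomarkers and parameters proposed as potential predictive biomarkers for immunotherapy" and says that they "will be correlated with pathological response and patient outcome". No arm is named or excluded.

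Section 2.6 (Data analysis) gives the method: "Correlation with outcomes will be evaluated with univariate regression models". It also says that no between-arm comparison is planned, that the biomarker work is meant to generate hypotheses, and that p ≤ 0.05 counts as significant without multiplicity adjustment.

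Section 2.3 (Treatments) fixes what each arm has received when response is read:
- Arm A: "mutated patients will receive (1) + (3) for 6 weeks", which is vemurafenib plus cobimetinib.
- Arm B: "mutated patients will receive (2) + (3) + (4) for 6 weeks", which adds atezolizumab and uses a different stated vemurafenib dose.
- Arm C: "WT patients will receive (3) + (4) for 6 weeks", which is cobimetinib plus atezolizumab.
- After surgery: "All patients will also receive atezolizumab 1200 mg intravenous every 3 weeks for 17 cycles after surgery".

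On timing, section 2.6 says: "A primary data analysis assessing the primary endpoint will be available after the neoadjuvant phase".

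**The concern.** The marker question concerns immunotherapy, but in arm A pathological response is fixed before the first dose of atezolizumab. Arm A can serve as a reference for that question. It cannot add information on how a marker relates to response under atezolizumab.

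A univariate model across all arms has neither an arm term nor a marker-by-arm term. Two things can then go wrong. A marker that matters only under atezolizumab is averaged with a group in which it does not matter, and may be missed. Or a marker of response to BRAF/MEK inhibition, or one that merely differs in level between BRAF-mutated and wild-type patients, reaches p ≤ 0.05 and is read as an immunotherapy marker. The Discussion names biomarker identification as one of the benefits expected from the study, so the direction of such leads matters even in exploratory work.

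**Working it through.** **1. Sizes.** Section 2.5 gives 27 patients in each of arms A and B and 34 in arm C: 27 + 27 + 34 = 88, the total in section 2.2. Arm A is 27/88 = 31% of patients. At the assumed pCR rates (60%, 60%, about 30%) the expected pCRs are 16.2 + 16.2 + 10.2 = 42.6, of which arm A supplies 16.2/42.6 = 38%. Arms B and C together have 27 + 34 = 61 patients.

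**2. Assumptions.** The article gives no marker effect or marker distribution, so these are assumed and varied. pCR stands for pathological response.

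**3. Attenuation, continuous marker.** Logistic simulation with logit P(pCR) = α(arm) + β(arm)·x, where x is standard normal, α = logit(0.60), logit(0.60), logit(0.30), and the test is a two-sided 5% Wald test. With 2,000 replicates the simulation error on a power near 50% is √(0.5 × 0.5/2000), about 1 percentage point. The odds ratio per SD is 2 in arms B and C throughout.

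| Odds ratio in arm A | Power, all arms, univariate | Power, all arms, arm term | Power, B + C, cohort term |
|---|---|---|---|
| 1.0 | 46% | 49% | 65% |
| 1.5 | 67% | 69% | 65% |
| 2.0 | 78% | 82% | 64% |

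In the first row the estimated odds ratios are 1.53, 1.61 and 2.1. An arm term corrects differences in level but not a different slope in arm A. In the second row the three analyses are about equal. In the third, dropping arm A costs power.

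**4. Attenuation, binary marker, from expected tables.** Marker-high in 50% of every arm; within-arm odds ratio 3 in B and C, 1 in A.
- B + C: high 16.82 pCR / 13.68 not; low 9.58 / 20.92. Odds ratio (16.82 × 20.92)/(13.68 × 9.58) = 2.69, power 46%.
- Adding arm A (8.1 / 5.4 in each marker group): high 24.92 / 19.08; low 17.68 / 26.32. Odds ratio (24.92 × 26.32)/(19.08 × 17.68) = 1.94, power 34%.
- If the odds ratio is 3 in arm A as well, all arms give 2.70 with 62% power, so there is no dilution.

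**5. Confounding by arm.** Suppose there is no association within any arm, but 60% of A and B and 30% of C are marker-high.
- High: 0.6 × 54 + 0.3 × 34 = 32.4 + 10.2 = 42.6 patients; pCR 32.4 × 0.6 + 10.2 × 0.3 = 22.5; not 20.1.
- Low: 21.6 + 23.8 = 45.4 patients; pCR 12.96 + 7.14 = 20.1; not 25.3.
- Crude odds ratio (22.5 × 25.3)/(20.1 × 20.1) = 1.41, from the 60% versus 30% pCR rates alone.

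**6. Misattribution.** In the simulation of step 3, a marker linked only to targeted-therapy response (odds ratio 2 in A and B, 1 in C) is significant in 40% of pooled univariate analyses and still in about 18% of B + C analyses, because arm B also receives both targeted drugs.

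**7. What the randomised pair can carry.** A marker-by-arm interaction in A versus B (27 each) has about 19% power for odds ratios 1 versus 2 per SD, and 16% for a binary marker with odds ratios 1 versus 3. The arms also differ in stated vemurafenib dose (960 versus 720 mg twice daily), so the contrast does not isolate atezolizumab.

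**The case against.** The strongest reply is that the article never says the arms are pooled. The trial is non-comparative and baseline characteristics are summarised by arm, so arm-by-arm correlation is equally compatible with the text and would show no dilution. Which arms enter an exploratory correlation may be settled in the full protocol or SAP, which are not shown. This stands: attenuation and confounding are conditional on pooling. What remains is that the article does state the purpose of the markers, the endpoint and the model, and as stated they do not fit together for arm A. Even a separate model in arm A says nothing direct about immunotherapy.

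A second reply is that dilution needs a marker effect near zero in arm A. CRP, LDH or blood counts may well relate to response under any treatment, and then excluding arm A loses power. This also stands and limits the size of the claim.

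A reader might infer more: that the association is diluted as a matter of fact, or that arm A makes it impossible to show that a marker is predictive. The documents support neither. Pooling is not stated, and arm A is the only arm without neoadjuvant immunotherapy, hence the reference that a predictive claim would need. The obstacles to such a claim are the univariate, non-comparative analysis and the small numbers. Nor does the plan promise one: it calls the markers only potentially predictive and the analysis exploratory.

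**Conclusion.** The point holds in a limited form. Arm A's pathological response precedes any atezolizumab, and the article does not set arm A apart when it relates immunotherapy markers to that response with univariate models.

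If the arms are pooled, an odds ratio of about 2.1 with 65% power in B and C can fall to 1.53 with 46%. That assumes an odds ratio of 2 per SD in B and C, none in A, and the protocol's planning pCR rates. The power advantage of leaving out arm A is gone once its odds ratio is about 1.5. Separately, differing marker levels between BRAF groups can produce a crude odds ratio such as 1.41 with no association in any arm.

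The correlations with recurrence-free and overall survival are not affected in the same way, since every arm is due adjuvant atezolizumab. The point is minor: the analysis is exploratory, and neither the primary endpoint nor the sample size depends on it.

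**What to change.** In sections 2.4 and 2.6, for the markers proposed as predictive for immunotherapy:

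- Estimate the association with pathological response in arms B and C, with a cohort term.
- Report arm A separately, as the reference without neoadjuvant immunotherapy.
- Include an arm term in any model that uses all arms.
- Word the results as associations.
- An A/B marker-by-arm estimate may be shown descriptively with its confidence interval, noting the difference in stated vemurafenib dose and the power of about 19%. It should not decide whether a marker is called predictive or prognostic; at that power a non-significant interaction does not show that a marker is merely prognostic.
- Correlations with recurrence-free and overall survival may keep all arms.

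The cost is analysis wording only, with no new data or patients. The downside is 61 instead of 88 patients in the main correlation, with lower power if the marker acts equally in arm A (64% against 78% for the pooled univariate model in the example above). The change reduces misattribution of a targeted-therapy marker but does not remove it, because arm B also receives vemurafenib and cobimetinib and arm C cobimetinib.

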### Sample size

2.5

This study is designed as a phase II randomized, non-comparative trial, with pCR as the primary endpoint. According to Amaria et al. (21), a 60% pCR rate may be assumed in arms A and B. A sample size of 27 patients in each arm is sufficient to give at least a 90% probability of rejecting a 30% pCR rate with an exact 5% one-sided significance test when the true pCR rate is 60%. The null hypothesis of a pCR of 30% will be rejected if a pCR is observed in at least 12 patients.

According to Huang et al. (25), a pCR rate of about 30% may be assumed in arm C. A sample size of 34 patients is sufficient to give an 80% probability of rejecting a pCR rate of 15% with an exact 5% one-sided significance test when the true pCR rate is 35%. The null hypothesis of a pCR of 10% will be rejected if a pCR is observed in at least 10 patients.

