### Selection of subjects

2.2

The study will enroll 88 subjects with surgically resectable *BRAF*-mutated and *BRAF* WT cutaneous melanoma. The detailed inclusion and exclusion criteria are summarized in **Table 1**.

Table 1Eligibility criteria for NEOTIM.

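### Arms A and B: rejecting the 30% null at 12 of 27 pCRs has a type I error of 8.0%, not the stated 5%; with 27 patients the cut-off has to be 13

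*Protocol article*

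**What the plan says.** The protocol article, section 2.5 (Sample size), sizes arms A and B separately and identically. The null pCR rate is 30% and the assumed true rate is 60%. The test is specified "with an exact 5% one-sided significance test", and on power the text says: "A sample size of 27 patients in each arm is sufficient to give at least a 90% probability". The decision rule follows: "The null hypothesis of a pCR of 30% will be rejected if a pCR is observed in at least 12 patients".

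Two other places bear on the reading. Section 2.2 (Selection of subjects) says: "The study will enroll 88 subjects". This equals 27 + 27 + 34, the three arm sizes, with nothing added for dropout. Section 2.6 (Data analysis) plans no comparison between arms and says: "No adjustment for multiple testing will be made". Each arm's test against its own null is therefore the only formal inference on the primary endpoint.

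**The concern.** An exact one-sided 5% test fixes the cut-off once the sample size and null rate are chosen: it is the smallest count whose upper-tail probability under the null is at most 0.05. The printed cut-off of 12 can therefore be checked directly against the printed 27 and 30%, and it appears one too low.

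This is the only numerical success criterion for the primary endpoint in two of the three arms. A cut-off that is too low errs in the anti-conservative direction, because an arm could be declared better than 30% on evidence that does not meet the plan's own standard. Section 2.6 also says of the primary endpoint: "Primary endpoint results will be reported as counts and rates with confidence intervals". A report could then show a rejected null beside an interval that still contains 30%.

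**Working it through.** **Inputs** (all from section 2.5): n = 27 per arm; null rate p0 = 0.30; alternative p1 = 0.60; exact one-sided α = 0.05; power at least 0.90; reject if X ≥ 12.

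**Formula.** With X ~ Binomial(n, p), the rule that rejects when X ≥ r has
- type I error = P(X ≥ r | n, p0) = Σ from k = r to n of C(n,k) p0^k (1 − p0)^(n−k)
- power = the same sum with p1 in place of p0.

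**Step 1: the printed rule and its neighbours at n = 27.**

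| Cut-off r | Type I error at 30% | Power at 60% |
|---|---|---|
| 12 (printed) | 0.0798 | 0.9663 |
| 13 | 0.0359 | 0.9257 |
| 14 | 0.0143 | 0.8553 |

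The printed rule exceeds 0.05 by a factor of 0.0798 / 0.05 = 1.6. A cut-off of 13 is the smallest that holds the level. It is also the only one that meets both stated properties, since 14 drops power below 90%.

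**Step 2: does another sample size make 12 valid?**

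| n | Type I error with r = 12 | Power with r = 12 |
|---|---|---|
| 24 | 0.0314 | 0.8857 |
| 25 | 0.0442 | 0.9222 |
| 26 | 0.0603 | 0.9482 |
| 27 | 0.0798 | 0.9663 |

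A cut-off of 12 holds 5% only for n of 25 or fewer. The total of 88 = 27 + 27 + 34 shows that 27 is the planned number per arm.

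**Step 3: does another test make 12 of 27 valid?** The text says exact, but as a check:
- Normal approximation: z = (12/27 − 0.30) / √(0.30 × 0.70 / 27) = 1.638, one-sided p = 0.0507.
- Mid-p: 0.0359 + ½ × (0.0798 − 0.0359) = 0.0579.

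Neither is at or below 0.05.

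**Step 4: is it a wording convention?** The same section also phrases the arm C rule as a minimum count, 10 of 34. Against the 15% null used there for the power statement, 10 is the correct exact cut-off: size 0.0240 and power 0.8045 at 35%, whereas 9 gives size 0.0587. The same phrasing therefore works for arm C and fails for arms A and B.

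**Step 5: what happens at exactly 12 of 27 (44.4%).**
- Exact one-sided p = 0.0798.
- Clopper-Pearson one-sided 95% lower bound (the lower limit of the two-sided 90% interval) = 28.0%, below the 30% null.
- At 13 of 27 that bound is 31.3%, above 30%.
- Probability of exactly 12 pCRs: 4.4% at a true rate of 30%, 15.3% at 45%, 4.1% at 60%.

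**The case against.** The strongest counter-argument is that the document shows an incompatibility between 12, 27 and an exact 5% test without showing which number slipped. A design with 25 patients and a cut-off of 12 is complete and valid (size 4.4%, power 92.2%), and 25 is the smallest sample size meeting both stated properties. The 27 could hide an unstated allowance of two patients. That is possible, but no dropout allowance is mentioned anywhere. The text says 27 is the number that gives the power, and the total of 88 uses 27. Keeping 27 and moving the cut-off is the reading that leaves everything else in the section true.

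Four smaller points deserve weight.
- The efficacy population is enrolled patients who received at least one dose, so the analysed number may not be 27. A cut-off of 13 is the exact 5% cut-off for 26 to 28 patients; 25 needs 12 and 29 needs 14. The corrected rule should therefore be tied to 27.
- The trial claims no family-wise error control. If both nulls were true and the arms independent, the chance of at least one false positive would be 1 − (1 − 0.0798)² = 15.3%, against 7.1% with 13. Two tests at exactly 5% would already give 1 − 0.95² = 9.75%. The defect is the per-arm 8.0% against 5%.
- The practical effect is confined to one outcome per arm, exactly 12 pCRs.
- The full protocol may already carry the right number. That is a reason to check it, but it does not make the published rule correct.

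None of these makes 12 of 27 an exact 5% test.

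**Conclusion.** The cut-off for arms A and B is wrong as written. With 27 patients and a 30% null, rejecting at 12 or more pCRs has a type I error of 7.98% per arm against the stated 5%. The smallest cut-off meeting the stated level is 13 (size 3.6%), and its 92.6% power at 60% satisfies the claim of at least 90%.

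The conclusion assumes only binomial counts and that 27 per arm is the analysed number. It should be corrected before the primary analysis: the rule decides the primary endpoint in two arms, and a change made after an arm had ended on 12 would look data-driven.

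**What to change.** In section 2.5, change the arm A and B rule to at least 13 of 27 patients with pCR, and state the attained size (3.6%) and power at 60% (92.6%). Add that, if the number analysed is not 27, the exact one-sided 5% binomial test at the actual number governs. Check the full protocol and the statistical analysis plan, neither of which was available for this review, for the same figure.

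It would also help to name an interval that agrees with the test: the Clopper-Pearson two-sided 90% interval, or the one-sided 95% lower bound. At 13 of 27 the 90% interval is 31.3% to 65.3%. A two-sided 95% interval would be 28.7% to 68.1% and would appear to contradict the rejection. This is a reporting recommendation; section 2.6 is not in error on this point.

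The cost is one number and a sentence or two. No patients are added. Power at 60% falls from 96.6% under the printed rule to 92.6%, still above the stated 90%.

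### Arm C is assumed to have a pCR rate of about 30%, but its 80% power is stated at 35% without explanation; at 30% the same rule has 59% power

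*Protocol article*

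**What the plan says.** All statements are in section 2.5, Sample size, of the Protocol article.

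- Expected rate for arm C, taken from a cited study: "a pCR rate of about 30% may be assumed in arm C".
- Power statement, in the next sentence: "A sample size of 34 patients is sufficient to give an 80% probability of rejecting a pCR rate of 15"%, the true rate being given as follows: "when the true pCR rate is 35"%.
- Decision rule: "The null hypothesis of a pCR of 10% will be rejected if a pCR is observed in at least 10 patients".
- For comparison, the paragraph on the *BRAF*-mutated arms: "a 60% pCR rate may be assumed in arms A and B". The power for those arms is then also computed at a true rate of 60%.

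The article gives no reason for moving from 30% to 35% in arm C.

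**The concern.** The assumed rate and the rate used for power normally coincide. Where they differ on purpose, the reason is normally given. Here they differ by 5 percentage points in consecutive sentences. A reader who takes the first sentence as the sponsor's expectation and the second as the assurance that goes with it will believe that the arm has an 80% chance of success if the regimen performs as expected.

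With 34 patients, 5 points matter a great deal. pCR is the primary endpoint, and the cut-off of 10 responders is the only success criterion stated for arm C. The chance of reaching it at the expected rate is therefore the figure on which the size of the arm is judged.

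**Working it through.** **Inputs** (all from section 2.5): n = 34; reject at 10 or more pCRs; null 15% in the power statement and 10% in the decision rule; exact one-sided 5% test; true rate 35% in the power statement; assumed rate about 30%.

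**Formula.** With X ~ Binomial(34, p), the chance of rejection is P(X ≥ 10 | p), the sum over k = 10 to 34 of C(34, k) p^k (1 − p)^(34 − k). At the null rate this is the size; at a true rate it is the power.

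**Step 1: reproduce the plan's figure.**
- Size at 15%: P(X ≥ 10 | 0.15) = 0.0240.
- A cut-off of 9 would give P(X ≥ 9 | 0.15) = 0.0587, above 5%. So 10 is the correct exact cut-off for a 15% null.
- Power at 35%: P(X ≥ 10 | 0.35) = 0.8045. The stated 80% is reproduced.

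**Step 2: the same rule at the assumed rate, and around it.**

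| True pCR rate | Power, n = 34, reject at ≥ 10 |
|---|---|
| 28% | 0.492 |
| 30% | 0.594 |
| 32% | 0.688 |
| 33% | 0.730 |
| 34% | 0.769 |
| 35% | 0.804 |

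At 30% the power is 59.4%, which is 80.4 − 59.4 = 21 points below the figure at 35%. The type II error is 1 − 0.594 = 0.406.

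**Step 3: does the 10% null explain the mismatch?** Power under a fixed cut-off does not depend on the null, so 59% at 30% stands under either null. With n = 34, an exact 5% test of 10% would reject at 7 or more (size 0.048, power 0.92 at 30%), which is not the stated rule. Under a 10% null the stated cut-off has size 0.0014. An exact design for 10% against 30% first reaches 80% power at n = 25 (reject at 6 or more, size 0.033, power 0.807). The cut-off of 10 is the exact 5% cut-off for the 15% null and not for the 10% null.

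**Step 4: what 80% power at 30% would take.** A search over n for an exact one-sided 5% test of 15% gives n = 48 as the smallest size with at least 80% power at 30% (reject at 12 or more, size 0.048, power 0.819). Exact power moves up and down with n. It stays at or above 80% for every n from 55 up to 129, the largest size checked.

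**The case against.** The strongest reply is that no calculation is wrong. The article claims 80% power at 35%, and that is what the design has. The sample size, the 15% null, the 35% alternative, the power and the cut-off fit together. A sponsor may power a study at a target above a historical rate, and the 30% rests on a source that cannot be consulted here. The rule itself is unambiguous, and its type I error is below 5% under either null (0.024 at 15%, 0.0014 at 10%). All of this stands. The fault lies in the planning justification and leaves the validity of the test untouched.

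Two parts of the defence do not hold. The word "about" does not close the gap, because power is still only 73% at 33% and reaches 80% only at about 35%. Nor does the text present 35% as a target: it offers 30% as the rate to assume and then uses another, while the preceding paragraph uses one rate for both purposes.

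A reader might infer more than the article supports. One such inference is that the 80% figure is an arithmetical error, or that arm C is simply underpowered. That would follow only if 30% was the intended alternative, and the article does not show whether 30% is a slip, 35% a deliberate target, or neither. Another is that the plan will treat a non-rejection in arm C as evidence of inactivity. It says no such thing: section 2.6, Data analysis, reports the primary endpoint as counts and rates with confidence intervals and plans no comparison among arms.

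**Conclusion.** The point holds as an unexplained mismatch between the planning premise and the powered alternative. The printed 80% is correct for a true rate of 35% and does not carry over to the 30% that the article itself assumes. There, power is 59%, so the arm would miss its criterion about 4 times in 10 if the regimen did exactly what is assumed.

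The 59% is conditional on a true rate of 30%, on 34 evaluated patients and on rejection at 10 or more. Reading "about 30%" as 28% to 33% gives a range of 49% to 73%. Which of the two rates was intended cannot be settled from the article. The 10% null in the decision rule is a separate inconsistency in the same paragraph and does not change these power figures.

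**What to change.** In section 2.5, and wherever the full protocol or analysis plan repeats the text:

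1. State which rate is expected in arm C and which is the powered alternative. Either label 35% as a deliberate target above the expected rate, with the reason, or correct the 30% if it is a slip.
2. Restate the operating characteristics along these lines: *n = 34, H0 15%, reject if 10 or more pCRs, exact size 2.4%, power 80% at 35% and 59% at 30%*.
3. In the same edit, reconcile the 10% null in the decision rule with the 15% in the power statement. The wording in item 2 uses 15% because the cut-off of 10 is the exact 5% cut-off for that null. If 10% was meant, the cut-off and the power statement must be reworked.

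The cost is wording, plus the disclosure of a less favourable power at the assumed rate. No extra patients are needed unless the sponsor wants 80% power at 30% against 15%. In that case the smallest exact design is n = 48 (reject at 12 or more, size 4.8%, power 82%). That is 48 − 34 = 14 more patients in arm C and takes the planned total from 88 to 102.

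### Arm C at 34 patients meets its stated 80% power but sits just past a jump in the exact cut-off; if the 15% null is confirmed, 33 patients with a cut-off of 9 would be more efficient, and the cut-off should follow the number treated

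*Protocol article*

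**What the plan says.** The Sample size section (2.5) of the protocol article states for arm C: "A sample size of 34 patients is sufficient to give an 80% probability of rejecting a pCR rate of 15" per cent, "with an exact 5% one-sided significance test when the true pCR rate is 35" per cent. The decision rule follows: "The null hypothesis of a pCR of 10% will be rejected if a pCR is observed in at least 10 patients". The rule therefore names a 10% null where the power statement names 15%. The same paragraph opens by assuming a pCR rate of about 30% for this arm.

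Selection of subjects (2.2) states: "The study will enroll 88 subjects". That equals 27 + 27 + 34, with no allowance for loss. Data analysis (2.6) restricts the efficacy population to enrolled patients who received at least one dose.

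**The concern.** In an exact binomial test the cut-off is a whole number, so power does not rise steadily with sample size. Each time the cut-off steps up by one, the actual type I error drops well below the nominal level and power falls with it. A sample size just after a step asks for one more patient and gives less power than the size just before it. At a 15% null, 34 is such a size.

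At stake is the chance that arm C misses a true 35% pCR rate: 19.6% as planned, against 13.2% with one patient fewer, both within the declared one-sided 5%. A second consequence is that a cut-off fixed at 10 is right only while the number analysed stays between 34 and 38.

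**Working it through.** **Inputs** (Sample size section): n = 34; cut-off r = 10; null p0 = 15%; alternative p1 = 35%; exact one-sided 5% test. The rate of about 30% from the same paragraph is used as a second scenario.

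**Formulas.** With X binomial(n, p):
- size = P(X ≥ r | n, p0)
- power = P(X ≥ r | n, p1)
- exact cut-off = the smallest r with P(X ≥ r | n, p0) ≤ 0.05

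**Step 1: reproduce the plan.** P(X ≥ 10 | 34, 0.15) = 0.0240 and P(X ≥ 10 | 34, 0.35) = 0.8045. The stated 80% is confirmed, and the size is within 5%.

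**Step 2: is 10 the right cut-off at 34?** P(X ≥ 9 | 34, 0.15) = 0.0587, above 5%. So 9 is not allowed and 10 is correct.

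**Step 3: neighbouring sample sizes, p0 = 15%.**

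| n | exact cut-off | size | power at 35% | power at 30% |
|---|---|---|---|---|
| 28 | 8 | 4.86% | 81.8% | 63.5% |
| 31 | 9 | 3.41% | 81.1% | 61.4% |
| 32 | 9 | 4.13% | 84.2% | 65.6% |
| 33 | 9 | 4.95% | 86.8% | 69.6% |
| **34** | **10** | **2.40%** | **80.4%** | **59.4%** |
| 35 | 10 | 2.92% | 83.5% | 63.5% |
| 36 | 10 | 3.51% | 86.2% | 67.5% |
| 37 | 10 | 4.19% | 88.5% | 71.1% |
| 38 | 10 | 4.95% | 90.4% | 74.5% |

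The cut-off is 9 for n = 29 to 33 and 10 for n = 34 to 38. From 31 to 38, n = 34 has the lowest power, and 37 patients are needed to pass the power available at 33. The difference between 33/9 and 34/10 is 86.8 − 80.4 = 6.4 points at 35% and 69.6 − 59.4 = 10.2 points at 30%.

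**Step 4: one of 34 enrolled patients is not dosed.** The analysed number is 33.
- Printed cut-off kept: P(X ≥ 10 | 33, 0.15) = 0.0195 and P(X ≥ 10 | 33, 0.35) = 0.7701, below the stated 80%.
- Exact cut-off for 33: P(X ≥ 9 | 33, 0.15) = 0.0495 and P(X ≥ 9 | 33, 0.35) = 0.8684.

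**Step 5: dependence on the null.** At p0 = 10% the exact cut-off for n = 34 is 7 (size 4.81%, power 97.8% at 35%), and the next jump comes at 35. Under that null, 34 is the last size before a jump and the efficiency point disappears. The printed cut-off of 10 fits 15%: at 10% its size would be only 0.14%.

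**The case against.** The strongest reply is that nothing in the power statement is wrong. It says 34 patients suffice for 80%, which they do, and it never claims that 34 is the smallest or most powerful choice. This stands. A reader might infer from the table that the sample size was miscalculated, and the reproduced 80.4% rules that out. A reader might also notice that 34/10 is the smallest exact design with 80% power at a one-sided 2.5% level and conclude that a stricter level was used; the document declares 5% and gives no sign of another level.

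Second, the gain is not free. Only the nominal level is the same for both designs: the actual type I error roughly doubles, from 2.40% to 4.95%, and the power comes from spending that error. This stands too. It is a trade-off within the level the protocol chose, and a team that prefers the lower error may reasonably keep 34/10.

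Third, test and interval may disagree. The Data analysis section reports the primary endpoint with confidence intervals but does not give their level. If they are two-sided exact 95% intervals (an assumption), the lower limit is 15.1% for 10 of 34 and 13.3% for 9 of 33. Rejection at exactly 9 of 33 would then come with an interval that still contains 15%. This is a fair cost of 33/9, conditional on that assumption.

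Fourth, 33 is at the edge: a 34th treated patient judged against 9 gives a size of 5.87%. This is true, and is why the cut-off has to move with the number treated. That rule helps the 34-patient plan equally.

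Fifth, optimising before the null is settled is premature. Agreed; the point is conditional on 15%.

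**Conclusion.** The point holds as a cheap efficiency improvement. Arm C as printed delivers its stated power. If 15% is the intended null, 33 patients with a cut-off of 9 would give 6.4 points more power at 35% and 10.2 points more at 30% with one patient fewer, in exchange for an actual type I error of 4.95% instead of 2.40%.

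The firmer part is the fixed cut-off. The analysis counts only dosed patients and the total of 88 allows for no loss, so a single untreated arm C patient would bring the printed rule to 77.0% power, although the declared 5% level would permit a cut-off of 9.

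The conclusion rests on three assumptions: the 15% null, the exact one-sided 5% test as declared, and a decision based on the number treated. It would not apply under a 10% null. The conflict between 10% and 15% is a separate and more serious matter. So is the rule for arms A and B, where rejecting at 12 of 27 against a 30% null has an exact size of 8.0%.

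**What to change.** 1. First reconcile the arm C null: state one value in both the power statement and the decision rule.
2. If it is 15%, either plan 33 patients with rejection at 9 or more pCRs (size 4.95%; power 86.8% at 35% and 69.6% at 30%), or keep 34 with rejection at 10 or more (size 2.4%; power 80.4% and 59.4%) and say that the lower actual error is accepted. Print the exact size and power of the chosen design.
3. In either case replace the fixed cut-off with a rule: reject if the number of pCRs is at least the smallest r for which P(X ≥ r | n treated, 15%) ≤ 5%. This gives 9 for 29 to 33 treated patients and 10 for 34 to 38.
4. If 33 is chosen, change the total from 88 to 27 + 27 + 33 = 87, provided arms A and B stay at 27.

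The cost is a few sentences in two sections that need correcting anyway for the null. Choosing 33 also means accepting an actual type I error close to the 5% limit and, if two-sided 95% intervals are reported, a possible disagreement between test and interval at exactly 9 of 33.
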